## Abstract

**Background:**

Internet based cognitive behavioural therapy (iCBT) has been demonstrated to be cost- and clinically effective. There is a need, however, for increased therapist contact for some patient groups. Combining iCBT with traditional face-to-face (ftf) consultations in a blended format (B-CBT) may produce a new treatment format with multiple benefits from both traditional CBT and iCBT such as individual adaptation, lower costs than traditional therapy, wide geographical and temporal availability, and possibly lower threshold to implementation. The primary aim of the present study is to compare directly the clinical effectiveness of B-CBT with face-to-face CBT for adult major depressive disorder.

**Methods/Design:**

The study is designed as a two arm randomised controlled non-inferiority trial comparing blended CBT for adult depression with treatment as usual (TAU). In the blended condition six sessions of ftf CBT is alternated with six to eight online modules (NoDep). TAU is defined as 12 sessions of ftf CBT. The primary outcome is symptomatic change of depressive symptoms on the patient-health questionnaire (PHQ-9). Additionally, the study will include an economic evaluation. All participants must be 18 years of age or older and meet the diagnostic criteria for major depressive disorder according to the Diagnostic and Statistical Manual of Mental disorders 4th edition. Participants are randomised on an individual level by a researcher not involved in the project. The primary outcome is analysed by regressing the three-month follow-up PHQ-9 data on the baseline PHQ-9 score and a treatment group indicator using ancova. A sample size of 130 in two balanced groups will yield a power of at least 80% to detect standardised mean differences above 0.5 on a normally distributed variable.

**Discussion:**

This study design will compare B-CBT and ftf CBT in a concise and direct manner with only a minimal of the variance explained by differences in therapeutic content. On the other hand, while situated in routine care, ecological validity is somewhat compromised by the controlled manner in which the study is conducted.

**Trial registration:**

ClinicalTrials.gov NCT02796573. Registered June 1st 2016. Currently recruiting participants.

## Background

Depression is a prevalent and disabling disorder with a high risk of relapse and large individual and societal costs [1–6]. Effective treatments exist [7], but there is a large gap between the need for and use of treatments [8]. Evidence based psychotherapies such as CBT, may help to bridge this gap. The reach of face-to-face (ftf) CBT is limited [9] however, which has led researchers to explore alternative modes of delivery of CBT such as Internet based guided self-help (iCBT) [10–16]. In spite of the evidence for the effect of iCBT, there is a need for increased therapist contact among some patient groups to overcome some of the shortcomings of iCBT [17–20].

Combining iCBT with traditional face-to-face consultations in a blended CBT format (B-CBT) may alleviate some of the difficulties associated with iCBT (such as lack of clinician contact), while still preserving some of the advantages of iCBT and face-to-face CBT alike. In B-CBT, online modules and face-to-face consultations are combined in one coherent treatment manual. This format could hold multiple benefits. Firstly, by providing face-to-face sessions, the therapist can individualise the therapy by taking the personal profile of the patient, the disorder, and possible co-morbidity into account. Secondly, since B-CBT only provides half the number of sessions as traditional face-to-face CBT, the capacity of the treating clinician is increased compared to traditional CBT. Third, the burden and cost of travel by the patient can be reduced. Fourth, the online modules are available at the time and place needed by the patients - and they can be re-viewed multiple times. Fifth, the inherently structured format of the online modules secures the same level of psycho-education and exercises to be delivered to all patients. Finally, one of the principal barriers for the uptake of iCBT seems to be skepticism from clinicians towards leaving the majority of therapy to a computer [21], a barrier possibly alleviated by the blended format in B-CBT.

Few studies have investigated the use of blended care combining internet based psychotherapeutic modules and face-to-face sessions into one coherent treatment manual [22–26]. Generally, however, they do indicate positive outcomes. In a randomised controlled trial conducted in primary care in Tromsø, Norway clinical psychologists delivered 30 min sessions following each online module [24]. They were able to document a significant difference with a moderate to large effect size (d = 0.65) on depressive symptoms (BDI-II) favouring blended care over waiting list. The intervention predominantly received positive evaluations suggesting acceptability and satisfaction with the treatment. Additionally, a qualitative study found that the face-to-face consultations increased motivation to persist with the iCBT programme [27]. Another recent example is the development and initial evaluation of a programme for B-CBT in The Netherlands. This was tested in an outpatient clinic of a specialised mental health care centre in Amsterdam. The study was designed as a feasibility study and included only nine patients. However, the patients perceived the intervention as positive although the authors rightly note that no conclusion can be derived from such a small sample [26].

## Aims and hypotheses

The primary aim of the present study is to compare the clinical effectiveness of blended cognitive behavioural therapy (B-CBT) for major depressive disorder (MDD) in adults with treatment as usual (TAU) defined as 12 sessions of face-to-face CBT. It is hypothesised that B-CBT will be no less clinically effective than TAU, and that it will be acceptable and satisfactory to patients and clinicians.

## Methods

### Design

The study is designed as a two arm randomised controlled non-inferiority trial comparing B-CBT for adult depression to treatment as usual (TAU) with an economic evaluation alongside. The present trial is part of the national project ENTER located and coordinated from the Center for Telepsychiatry and is additionally affiliated with the EU-study E-COMPARED [28].

### Participants

#### Inclusion criteria

All participants must be 18 years of age or older and meet the diagnostic criteria for major depressive disorder according to the Diagnostic and Statistical Manual of Mental disorders 4th edition (DSM-IV) [29]. Additionally, the participants must score ‘5’ or higher on the Patient Health Questionnaire-9 (PHQ-9) [30].

#### Exclusion criteria

Patients will be excluded in case of current high risk of suicide or if they suffer from a co-morbid substance dependence, bipolar affective disorder, psychotic illness, or obsessive compulsive disorder. Additionally, participants will be excluded if they currently receive psychological treatment for depression in primary or specialised mental health care. Finally, they will be excluded if they are unable to comprehend Danish or if they do not have access to a PC and Internet connection.

### Recruitment

Participants are recruited from the Centre for Telepsychiatry in specialised mental health care at the Mental Health Services of the Region of Southern Denmark, where they are referred to the study by clinicians. Initially, however, patients are self-referred to the Centre for Telepsychiatry.

The diagnosis will be confirmed by telephone administered interviews using the International Neuropsychiatric Interview version 5.0 (M.I.N.I.) [31] administered via telephone by trained masters students in psychology. Additionally, the participants are asked for permission from the research team to obtain the results of the PHQ-9 questionnaire from their application form to minimise the burden on the patients. Patients are asked to keep eventual antidepressant medication stable during treatment. If changes should occur, they are asked to report it.

### Randomisation and blinding

An independent researcher who is not involved in the trial performs the randomisation (centrally from Amsterdam) at an individual level, stratified by country after eligibility and baseline measurement. A computerised random number generator (Random Allocation Software) will be applied with an allocation ratio of 1:1. Block randomisation will be used with variable block sizes that vary between eight and fourteen allocations per block.

The assessors for eligibility will be blinded to group allocation. During treatment, blinding of participants and clinicians are naturally impossible. Researchers and statisticians involved in the analyses will be blinded to group allocations. The groups will be numbered in the dataset without revealing which treatment was given. The questionnaires administered solely to the B-CBT group will be analysed in a separate dataset.

### Interventions

#### Blended treatment (B-CBT)

B-CBT combines (blends) six individual face-to-face CBT sessions with six to eight online CBT modules delivered through an Internet based treatment programme. The face-to-face consultations will be provided by a psychologist at the Centre for Tele-Psychiatry.

The programme is a recently developed iCBT programme (NoDep) based on CBT for depression which includes six mandatory modules and two optional ones. The core components of the mandatory modules are: psycho-education, cognitive restructuring, behavioural activation, behaviour experiments, and relapse prevention. The optional modules comprise: coping with rumination, and restructuring of core beliefs. The decision whether to add any optional modules are taken jointly by the patient and the psychologist based on patient needs, motivation, and possible time constraints. See Table 1 for an overview of the intervention. All modules are delivered via multimedia elements including video, audio, interactive exercises, calendar, and pdf summaries. The program has a build in workflow predetermining the order in which the modules are presented. All data is stored in Europe and is encrypted during storage and transmission.

**Table 1 Tab1:** Interventions

Session number	Format of delivery	Content	Example of exercise
	B-CBT		
1	F2F	Introduction and psychoeducation about depression and the treatment	Find a helper
2	Online module	Introduction to the programme, psychoeducation about depression, and goals for the treatment	Problem- goal list
3	F2F	Idiosyncratic model of the disorder	Cognitive case formulation
4	Online module	Psychoeducation about behaviour in depression	Activity registration
5	F2F	Accordance between personal values and behaviour. Introduction to cognitive restructuring.	Simple exercise for cognitive restructuring
6	Online module	Changing behaviour based on activity registration and personal values	Activity planning
7	F2F	Psychoeducation about negative automatic thoughts and cognitive restructuring.	Cognitive restructuring exercise
8	Online module	Psychoeducation about negative automatic thoughts and cognitive restructuring.	Cognitive restructuring exercise
9	F2F	Psychoeducation about behavioural experiments. Decision is made whether to include one or both of the extra modules	Behavioural experiment
10	Online module (A, B)	Behavioural experiments. (A: psychoeducation about core beliefs, B: coping with rumination)	Behavioural experiment (A: challenge core beliefs, B: test three techniques for coping with rumination)
11	F2F	Summing up, relapse prevention	Continuation of preferred exercises
12	Online module	Summing up, relapse prevention	Personal relapse prevention plan
	TAU		
1	F2F	Introduction and psychoeducation about depression and the treatment	Find a helper
2	F2F	Psychoeducation and goals for the treatment	Problem- goallist
3	F2F	Idiosyncratic model of the disorder	Cognitive case formulation
4	F2F	Psychoeducation about behaviour in depression	Activity registration
5	F2F	Accordance between personal values and behaviour. Introduction to cognitive restructuring.	Simple exercise for cognitive restructuring
6	F2F	Changing behaviour based on activity registration and personal values	Activity planning
7	F2F	Psychoeducation about negative automatic thoughts and cognitive restructuring.	Cognitive restructuring exercise
8	F2F	Psychoeducation about negative automatic thoughts and cognitive restructuring.	Cognitive restructuring exercise
9	F2F	Psychoeducation about behavioural experiments.	Behavioural experiment
10	F2F	Psychoeducation about core beliefs or continue working on behavioural experiments	Challenge core beliefs or behavioural experiment
11	F2F	Psychoeducation about rumination or beginning of relapse prevention	Test three techniques to cope with rumination or start personal relapse prevention plan and continuation of preferred exercise
12	F2F	Summing up, relapse prevention	Personal relapse prevention plan

For technical support to the participants, the existing procedures at Internetpsykiatrien are used, which consists of two levels: the first is handled by the clinicians, the second goes through an error report system to the company providing the software (Context Consulting).

### Treatment as usual (TAU)

TAU will be defined as 12 sessions of face-to-face CBT including the same core components as the B-CBT condition. Additionally, interventions on core beliefs and rumination can be included according to the same criteria as in the B-CBT condition. See Table 1 for an overview of the intervention.

Patients in either condition is monitored weekly for symptoms of depression including suicidal ideation and -intent. Should any participant deteriorate or show signs of suicidal intent, an assessment interview will be conducted and the patient will be discontinued if necessary and referred to relevant treatment.

### Adherence

Participants will receive automated sms and/or e-mail reminders of homework assignments and questionnaires. In case a patient is inactive for more than two days without prior agreement with the treating psychologist, the patient is contacted via e-mail and telephone. Additionally, a computer is setup at the clinic, for participants to engage with the online programme in case they are for some reason not able to do so at home. This includes lack of adherence even if they do not suffer technical difficulties.

#### Treatment fidelity

All therapists are clinical psychologists. To ensure treatment fidelity (1) detailed treatment manuals, one for each treatment condition, has been developed to guide therapists through the treatment, (2) regular supervision is provided by the research coordinator to prevent drift, (3) therapists will register the number of sessions, the frequency of the sessions, the main strategies used in each sessions and the length of each contact, and finally (4) all sessions will be audio recorded and approximately 5% of the sessions in each condition will be randomly selected and evaluated by an external CBT expert (Fig. 1).

**Fig. 1 Fig1:**
[figure not shown]
Patient flow diagramme

### Outcome measurements

Baseline measures will be administered after consent has been granted prior to randomisation. The participants will be followed up three-, six-, and twelve months after baseline measurement. In case of drop-out, a short questionnaire regarding reasons for drop-out will be administered. All questionnaires for the participants will be administered online. A secure web application for building and managing online surveys (RedCap) will be used for all questionnaire packages except the weekly monitoring for the B-CBT group, which will be administered from within the treatment programme. See Table 2 for an overview of measurements and time points. Data is stored by Odense Patient data Exploratory Network. Data is managed by a local data manger with training and prior experience in datamangement. The datamanager quality checks data continuously. Data is collected, transferred, and stored securely electronically and is approved by the Danish Data Protection Agency (J.nr.: 14/26634 Reg. nr.: 2008-58-0035).

**Table 2 Tab2:** Overview of measurements

Variable	Instrument	Items	Time (mins)	Screening Baseline	Weekly	3 months	6 months	12 months
Questions taken from participants								
Demographics		n/a	1	X				
Current treatment		n/a	2	X				
Diagnostic interview	M.I.N.I.	n/a	15	X				X
Depressive symptoms	QIDS-SR16	16	3	X	Item 12	X	X	X
	PHQ-9	9	2	X	X	X	X	X
Treatment preference		1	1	X				
Patient expectancy	CEQ	8	2	X				
Working alliance	WAI-SF	12	3			X		
Technology alliance	TAI-SR^a^	12	3			X		
Client satisfaction	CSQ-8	8	3			X		
Satisfaction with the online programme	SUS^a^	20	3			X		
Drop-out	Number of sessions completed - data extraction	n/a	0				X	
	Patients reason for drop-out. Questionnaire	3	2				X	
Questions taken from therapists								
Working alliance	WAI-SRT	12	3			X		
Satisfaction with the online programme	SUS^b^	20	3			X		

^a^Offered to condition receiving blended treatment only, ^b^Has to be completed once per therapist after completion of the first treatment

#### Primary outcome

The Patient Health Questionnaire-9 (PHQ-9) [30] will be used as primary outcome measurement to evaluate change in severity of depressive symptoms. It is a nine items questionnaire which can be used to screen and diagnose patients with depressive disorders. The nine items are each scored on a 0–3 point scale with a total score ranging from 0–27 with higher scores indicating more severe depression. The PHQ-9 has been shown to have good psychometric properties [32].

#### Secondary outcomes

The Quick Inventory of Depressive Symptomatology Self-Report (QIDS-16-SR) [33] is used in addition to the PHQ-9 because it is a promising questionnaire for assessing depressive symptoms especially in specialised mental health care, whereas the PHQ-9 is developed for use in primary care. The QIDS-16-SR is a questionnaire that screens for depressive symptoms and assesses depression severity. It consists of 16 items each scored on a 0–3 point scale and includes symptom domains of MDD based on DSM-IV. The QIDS-16-SR has shown good psychometric properties [33, 34].

The Client Satisfaction Questionnaire (CSQ-8) [35] is used to measure the patients’ satisfaction with the treatments. The questionnaire consists of eight items measured on a four point scale with total scores ranging from 8–32 and has shown good psychometric properties [36]. Clinician satisfaction with the treatment will be assessed by the short form of the Client Satisfaction Questionnaire including only the three core questions of the csq-8.

To measure the patients’ expectancy and judgement of credibility of the treatments the Credibility and Expectancy Questionnaire (CEQ) [37] is used. The CEQ is a two part questionnaire measuring credibility and expectancy respectively. Both factors have been shown to be stable across different populations, with high internal consistency within each factor [37].

To indicate whether a difference is seen in the therapeutic alliance the short version of the Working Alliance Inventory (WAI-SR) is used. WAI-SR is a 12 item self-report questionnaire with responses on a five point Likert scale ranging from 1 (never) to 5 (always) [38, 39]. The questionnaire covers three dimensions of working alliance: (1) therapeutic goals, (2) tasks, and (3) bond and the sub scales have demonstrated good internal consistencies [40]. Both the patient and the ten items therapist version of the questionnaire will be administered. The alliance between the patient and the programme will be assessed with the WAI Online Therapy (TAI)(Labpsitec, 2014).

Finally, to measure the patients’ perception of the usability of the software, the System Usability Scale (SUS) [41] is used. It is a simple ten item scale giving a global view of subjective assessments of usability of a technology system. All items are measured on a 5-point scale ranging from ‘strongly disagree’ to ‘strongly agree’. Total SUS scores have a range from 0–100. The questionnaire has been found to be reliable and robust [42].

## Sample size and statistical analyses

The primary outcome is analysed by regressing the three-month follow-up PHQ-9 data on the baseline PHQ-9 score and a treatment group indicator. We will use an ancova model for this purpose. Missing values are handled using a full-information maximum likelihood estimator. In case of dropout, we will use the last observed values in a supplementary intention-to-treat analysis. Missingness sensitivity will be assessed with a best-/worst-case comparison, where missing values are replaced with the minimum and maximum values observed at follow-up.

The primary hypothesis is that the blended care intervention will be no less effective than the TAU intervention in reducing depression symptoms. A sample size of 130 in two balanced groups will yield a power of at least 80% to detect standardised mean differences above 0.5 on a normally distributed variable. This equivalence interval is slightly narrower than other estimates of minimally clinically important differences [43].

In addition, we will compare the development of PHQ-9 in the two groups using the weekly measurements in a mixed effects model. We will model the individual trajectories as random slopes, and then let the treatment group predict the slopes. Significant slope differences between groups will indicate either faster or slower treatment effects in the blended care group. In case of non-normal data, we will use an appropriate measure of transformation or a generalised linear model. Variables with significant variations between groups at baseline are introduced as control variables.

Secondary outcomes will be analysed using t-tests or a rank sum test. Where appropriate, differences between baseline and follow-up scores are used as outcomes instead of only comparing the follow-up score.

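### The trial claims non-inferiority, but the article never ties its 0.5 SD interval to the ANCOVA group coefficient, so its wording permits an ordinary difference test

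*Protocol article*

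**What the plan says.** Under Design the article states: "The study is designed as a two arm randomised controlled non-inferiority trial". The section on sample size and statistical analyses gives a hypothesis that runs in one direction: "The primary hypothesis is that the blended care intervention will be no less effective than the TAU intervention in reducing depression symptoms". Aims and hypotheses says the same.

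The primary analysis, in that section and in the Abstract, is a regression model: "The primary outcome is analysed by regressing the three-month follow-up PHQ-9 data on the baseline PHQ-9 score and a treatment group indicator". The text names it as an ANCOVA and attaches no comparison with a margin.

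The sample of 130 "will yield a power of at least 80% to detect standardised mean differences above 0.5 on a normally distributed variable". The following sentence gives the same 0.5 another role: "This equivalence interval is slightly narrower than other estimates of minimally clinically important differences [43". The Abstract repeats the power sentence but not the one about the interval.

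**The concern.** One number, 0.5 SD, is asked to serve three different tests:

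- **Difference test.** Power to detect 0.5 is the chance of rejecting a null of no difference when the true difference is 0.5.
- **Equivalence test.** An equivalence interval is two-sided: the difference must be shown to lie between -0.5 and +0.5.
- **Non-inferiority test.** The label and the hypothesis need one bound only: a B-CBT deficit of 0.5 or more must be excluded.

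The ANCOVA can serve any of these, depending on what is done with its group coefficient, and the article does not say. If the difference-test wording were followed, lack of significance would be the only result available to support the hypothesis. That puts the error control in the wrong place: a smaller sample, more dropout and a noisier outcome would each make a favourable reading more likely. The trial's main conclusion depends on which test is meant.

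**Working it through.** **Inputs.** From the article: 130 patients, 1:1 allocation, so 65 per arm; standardised difference 0.5; power at least 80%. Higher PHQ-9 is worse, so a positive B-CBT minus TAU difference means that B-CBT is worse. Assumed here because the article does not give them: two-sided 0.05 (equal to one-sided 0.025), the baseline-outcome correlation r, and the loss to follow-up. Differences are in units of the follow-up SD.

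**Step 1: the article's own figure.** SE = sqrt(2/65) = 0.175. Power of a difference test at 0.5 = Φ(0.5/0.1754 - 1.96) = Φ(0.890) = 81.3% (80.8% by the noncentral t). The stated figure of at least 80% is reproduced.

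**Step 2: the same N under the other two readings, true difference zero.**

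- Non-inferiority, margin 0.5, one-sided 0.025: Φ(0.5/0.1754 - 1.96) = 81.3%, the same expression. Both formulas need 63 per arm by the normal approximation.
- Two-sided equivalence within ±0.5: 2Φ(0.5/0.1754 - 1.645) - 1 = 77.2% at one-sided 0.05, and 62.7% at one-sided 0.025.

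So the stated power holds for a difference or a non-inferiority test, but not for a literal equivalence test.

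**Step 3: where the decisions diverge** (65 per arm, no covariate gain).

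- An observed deficit is non-significant up to 1.96 × 0.1754 = 0.344 SD. Its upper 95% limit is then 0.688 SD, well beyond 0.5.
- A margin rule needs an observed deficit below 0.5 - 0.344 = 0.156 SD.
- Observed deficits between 0.156 and 0.344 SD are therefore non-significant, yet do not show non-inferiority.

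**Step 4: how often a B-CBT truly worse by 0.5 SD would pass.** If non-significance counted as support, the probability is Φ(1.96 - 0.5/SE), with SE = sqrt(2/n) × sqrt(1 - r²). For the 20% loss, n is taken as 52 per arm.

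| n per arm | r (assumed) | SE | Passes if non-significance counts | Passes under margin rule |
|---|---|---|---|---|
| 65 | 0 | 0.175 | 18.7% | 2.5% |
| 65 | 0.3 | 0.167 | 15.2% | 2.5% |
| 65 | 0.5 | 0.152 | 9.2% | 2.5% |
| 65 | 0.6 | 0.140 | 5.4% | 2.5% |
| 52 (20% loss) | 0 | 0.196 | 27.8% | 2.5% |
| 52 (20% loss) | 0.5 | 0.170 | 16.3% | 2.5% |

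The last row with r = 0.5: sqrt(2/52) × sqrt(0.75) = 0.170; 0.5/0.1698 = 2.944; Φ(1.96 - 2.944) = 16.3%.

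**Step 5: power under the margin rule, true difference zero.** With 65 per arm and complete data: 81.3% at r = 0, and 84.8%, 90.8% and 94.6% at r = 0.3, 0.5 and 0.6. With 52 per arm and r = 0 it is 72.2%.

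**The case against.** The strongest reply is that this is a condensed article. The confidence limit, alpha, sidedness and conversion to PHQ-9 points are commonly left to a full protocol or analysis plan, which is not shown. A margin-like value is present, stated just after the hypothesis, and the ANCOVA coefficient with its confidence interval is exactly what a non-inferiority comparison uses. All of that stands: the model is not wrong, and the missing detail alone would not be a finding. What remains is that the printed sentences disagree with one another. A later plan would have to choose among three tests, and one of them does not reach the stated power.

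Three stronger readings are tempting but unsupported:

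- **That a non-significant coefficient will be read as success.** No sentence says so. The only PHQ-9 rule phrased through significance concerns slopes in the additional weekly mixed model. The wording permits the reading and no more.
- **That the SD converting 0.5 to points is left until the data are seen.** The article is silent on which SD applies. Silence does not show a post-hoc choice.
- **That 0.5 is too wide because it takes up most of the one effect size cited.** That figure is a "moderate to large effect size (d = 0.65) on depressive symptoms (BDI-II) favouring blended care over waiting list". It comes from another scale and is the effect of blended care, not of 12-session face-to-face CBT, against an inactive control. It cannot show how much of TAU's benefit a 0.5 margin preserves. The article's own basis for 0.5 is a cited source that is not at hand.

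**Conclusion.** The concern holds as an inconsistency in the stated text. A trial labelled non-inferiority describes an ordinary ANCOVA group comparison, words its power as for a difference test, calls the same 0.5 an equivalence interval, and never applies it to the coefficient.

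The size is conditional on non-significance being taken as support. In that case a true deficit of 0.5 SD would pass between about 5% and 19% of the time with complete data, depending on the gain from baseline adjustment. With an assumed 20% loss it would pass about 28% of the time with no covariate gain and 16% at a correlation of 0.5. A margin rule holds this at 2.5%. The upper figures ignore the planned baseline adjustment and should not be quoted alone. Alpha, correlations and loss are assumptions. The sample size itself is not in error.

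**What to change.** Before unblinding, in the protocol or analysis plan:

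1. Name 0.5 SD as the non-inferiority margin and fix it in PHQ-9 points, stating the pre-specified SD used. For illustration only, an SD of 5 to 6 points (not given in the article) would make it 0.5 × 5 = 2.5 to 0.5 × 6 = 3.0 points.
2. State the decision rule: conclude non-inferiority only if the upper limit of the two-sided 95% confidence interval for the adjusted difference (B-CBT minus TAU, three-month PHQ-9) is below that margin.
3. State that a non-significant group coefficient is not evidence of non-inferiority.
4. Replace the term *equivalence interval* with *non-inferiority margin*. Restate the power as power to exclude the margin at a true difference of zero: about 81% with 65 per arm, complete data and one-sided 0.025.

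The cost is wording only. The ANCOVA, the data collected and N = 130 are unchanged.

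### As written, full-information maximum likelihood adds nothing to the primary ANCOVA: patients without a 3-month PHQ-9 do not inform the treatment estimate, although weekly PHQ-9 could be used

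*Protocol article*

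**What the plan says.** All analysis statements are in the Protocol article, section Sample size and statistical analyses.

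- Primary model: "regressing the three-month follow-up PHQ-9 data on the baseline PHQ-9 score and a treatment group indicator". The next sentence adds: "We will use an ancova model for this purpose".
- Missing data in that model: "Missing values are handled using a full-information maximum likelihood estimator". No auxiliary variable and no second outcome is named.
- Patients who drop out: "we will use the last observed values in a supplementary intention-to-treat analysis". A best-/worst-case analysis, using the lowest and highest follow-up values observed, is planned as a sensitivity check.
- Weekly scores: "In addition, we will compare the development of PHQ-9 in the two groups using the weekly measurements in a mixed effects model". This is a separate model in which treatment group predicts individual slopes.

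Two points from the section Outcome measurements matter. The baseline covariate should be essentially complete: "Baseline measures will be administered after consent has been granted prior to randomisation". Table 2 lists PHQ-9 weekly as well as at 3, 6 and 12 months, and the section Treatment as usual (TAU) says that both arms are monitored weekly for depressive symptoms.

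**The concern.** The sentence on full-information maximum likelihood reads as if the primary result makes use of patients whose 3-month score is missing. Likelihood methods do that only when such patients have other modelled variables that carry information about the missing outcome. Here the only other variables are the two predictors, on which the model already conditions.

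The method's validity then rests on a narrow assumption: among patients with the same baseline PHQ-9 in the same arm, those with and without a 3-month score have the same expected outcome. In a depression trial, whether a patient answers at 3 months may well depend on how the preceding weeks went. The arms differ in face-to-face contact (6 sessions against 12), so that dependence need not be the same in both. The non-inferiority conclusion turns on one confidence limit, and a shift of a fraction of a point to about two thirds of a point could decide it. The weekly PHQ-9 would allow a weaker assumption, but it is kept out of the primary model.

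**Working it through.** **The plan's own figure.** The article states at least 80% power for a standardised difference of 0.5 with 130 patients. Alpha is not stated; assume two-sided 0.05. With 65 per arm, 0.5 × √(65/2) − 1.96 = 2.850 − 1.960 = 0.890, so power is Φ(0.890) = 81.3% (80.8% by the noncentral t). The figure reproduces if all 130 outcomes are observed.

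**Why the two estimators coincide.** Write y for 3-month PHQ-9, x for baseline PHQ-9 and g for arm. Each patient's likelihood contribution is:

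- y observed: f(x | g; φ) × f(y | x, g; β, σ²)
- y missing: f(x | g; φ) × ∫ f(y | x, g; β, σ²) dy = f(x | g; φ) × 1

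β, which contains the treatment effect, appears only in the terms with y observed. Maximising over β is least squares on those patients, whether or not x is modelled jointly.

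**Numerical check.** Simulated data, N = 130, 39 outcomes missing:

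| Estimator | Treatment coefficient | Baseline slope |
|---|---|---|
| OLS, observed outcomes only | −0.29372 | 0.55058 |
| Maximum likelihood, conditional on x and g | −0.29372 | 0.55058 |
| Maximum likelihood, y and x jointly | −0.29372 | 0.55058 |
| Maximum likelihood with one weekly score w added | −0.66122 | 0.61415 |

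A second dataset (N = 130, 41 missing) gave coefficients 0.4507, 0.6680 and 0.4139 by both least squares and joint maximum likelihood.

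**Why a weekly score changes this.** If y = b0 + b_g g + b_x x + b_w w + error and w = a0 + a_g g + a_x x + error, the treatment effect on y given x is b_g + b_w × a_g. The b terms come from patients with y observed, but a_g comes from everyone with w, including those without y. The last table row shows only that the estimate moves. The full-data coefficient in that dataset was −0.278, so one dataset cannot show which estimator is better. Repetition can: over 400 runs with a true effect of 0, 24% and 31% missing, and missingness depending on w in one arm only, the mean estimate was −0.54 points as written and 0.00 with w in the likelihood. The run-to-run SD was 0.76, so the Monte Carlo error is about 0.76/√400 = 0.04.

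**Size and direction.** The document gives no dropout rate or mechanism, so everything here is assumed: true B-CBT deficit 2.57 points, 3-month SD 5.6, correlation with the 3-month score 0.47 for baseline and 0.75 for week 6. Selective means that non-improvers at week 6 are likelier to have no 3-month score.

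| Scenario | Estimate as written | Difference from 2.57 |
|---|---|---|
| Selective in B-CBT only, 25% missing per arm | 1.86 and 1.93 (two set-ups) | −0.71 and −0.64 |
| Selective in both, 30% B-CBT, 15% TAU | 2.14 | −0.43 |
| Selective in B-CBT only, 10% missing | 2.33 | −0.24 |
| Same mechanism in both, 25% each | 2.56 | −0.01 |
| Selective in both, 15% B-CBT, 30% TAU | 2.95 | +0.38 |
| Selective in TAU only | 3.20 | +0.63 |

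The 1.93, 2.33, 2.56, 2.95 and 3.20 also assume a baseline to week-6 correlation of 0.5 and logistic dropout on change to week 6. A model with the weekly scores was fitted in the settings giving 1.86 and 2.14 and returned 2.56 in both.

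**The case against.** The strongest reply accepts the algebra and limits what may be built on it. Most of it stands.

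- **Not an analysis of treatment completers.** A reader might infer this from "the patient will be discontinued if necessary and referred to relevant treatment" in the section Treatment as usual (TAU). That sentence concerns stopping treatment. Follow-up at 3, 6 and 12 months is planned online for participants, and nothing says that a discontinued patient loses it. Someone who stops treatment but answers at 3 months stays in the primary analysis.
- **Patients without a 3-month score are not ignored.** They enter the last-observed-value analysis, where the last value would naturally be a weekly PHQ-9, and the best-/worst-case analysis. Neither repairs the primary estimate: the first assumes no change after the last score, and the second substitutes extremes. Neither gives a missing-at-random estimate that uses the weekly course.
- **The word supplementary proves little.** A reader might infer that the primary analysis is not by intention to treat. The word describes the last-value analysis. No sentence excludes patients or analyses them other than as allocated.
- **The bias has no known direction.** A reader might infer that it favours non-inferiority. That holds only if B-CBT loses poor responders more selectively or in greater number. The reverse pattern works against non-inferiority, and the document supports neither.
- **Auxiliary variables may be in a statistical analysis plan.** The article neither lists nor rules them out, and a plan that includes them would settle the matter. The article does, however, specify the model's variables and the estimator, and with those the estimator cannot do what the sentence suggests.
- **The estimator need not be wholly idle.** Baseline control variables may be added, and some could be incomplete. Maximum likelihood would then keep patients with a missing covariate, but it would still not use the treatment course of those with a missing 3-month score.

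**Conclusion.** The point stands in this form: for the model as stated, full-information maximum likelihood and least squares on patients with an observed 3-month PHQ-9 give the same treatment estimate. This identity needs only a single outcome, essentially complete predictors and no auxiliary variables; it does not depend on any simulated parameter. The primary estimate is unbiased if missingness depends only on baseline PHQ-9 and arm, and it can be biased otherwise.

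The size is not known. In the assumed scenarios the bias ran from about −0.7 to +0.6 points around a true deficit of 2.57, and it vanished when mechanism and dropout rate were the same in both arms. These figures show that the issue can matter, not that it will. The plan should be changed because a better method is available from data already being collected.

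**What to change.** Keep the 3-month between-group contrast as the primary estimate, but estimate it from all randomised patients as allocated, with weekly and 3-month PHQ-9 in one likelihood. Either form would do:

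- a repeated-measures model of weekly and 3-month PHQ-9, adjusted for baseline, with the contrast taken at 3 months; or
- the stated ANCOVA by full-information maximum likelihood, with a few weekly PHQ-9 scores (for example weeks 4 and 8 and the last) as arm-specific auxiliary variables. A small number keeps the model estimable with 130 patients.

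State that the confidence limit compared with the non-inferiority margin comes from this model. The last-observed-value and best-/worst-case analyses can remain in their present roles.

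The cost is a change of wording and modest extra modelling. No new data are needed, but the B-CBT weekly scores sit in the treatment programme rather than the survey system and must be linked for all patients. The revised analysis still assumes missing at random, now given the weekly course as well, so a sensitivity analysis remains necessary.
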